### Sample size

The sample size calculation is based on a comparison between the intervention group and the placebo-controlled group. The mean duration of all symptoms for the common cold was estimated to be 7 ± 3 days [7, 25], and reduction in the duration of all symptoms by 2 days is assumed to be clinically significant. Using Power Analysis and Sample Size (PASS) 11.0 with 90% power (1–β) and α = 0.05 (two-sided), the sample size needs to be 48 cases for each group. Considering a drop-out of 20%, we decided to recruit 60 subjects in each group. According to the latest edition of Provisions for Drug Registration issued by the CFDA on phase II clinical trials, the total sample size was set to be 240 patients.

### Data management and statistical analysis

The Drug Clinical Research Center of Shanghai University of TCM is in charge of data statistical analysis. The data entry will be performed by two independent data administrators using the software EpiData 3.1 based on the CRFs, which should have been checked and reviewed for accuracy and consistency by the clinical research associate (CRA) and investigators. Finally, the database will be locked and analyzed under the agreement and confirmed review of the sponsor, principal investigator, and statistician.

The full analysis set (FAS), in which patients should be dosed with LJGMG or placebo at least once with clinical observation record in the study, is the primary analysis set according to the intention-to-treat (ITT) principle using the last observation carried forward (LOCF) approach for missing values. All subjects without any major protocol deviations will be included in the per-protocol set (PPS). An efficacy assessment will be carried out using the FAS and PPS. A safety evaluation will be conducted for subjects who have experienced at least one study visit and have safety data, which is defined as the safety set (SS).

All continuous and normally distributed data are presented as mean ± standard deviation, and median with range for non-normal data. Categorical data are summarized by frequency counts and percentages. Baseline balance among groups will be conducted by performing a chi-squared test or an analysis of variance (ANOVA). Time to all symptoms’ clearance, time to primary symptoms and each secondary symptom disappearance, time to fever relief, and time to fever clearance will be estimated and compared by the log-rank test. A Kaplan-Meier survival curve will be constructed, and the median time will be provided separately for each group with a two-sided 95% confidence interval. Comparisons among groups of TCM symptom and sign scores will be conducted using ANOVA and the Bonferroni method. All data will be processed by a professional statistician using SAS 9.2 software (SAS Institute, Cary, NC, USA); a two-sided *P* value of <0.05 is considered to be statistically significant.

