This phase II clinical trial is well designed to evaluate the efficacy and safety of LJGMC compared with placebo in patients with CCWHS. Additionally, it is expected to find a dose-efficacy relationship and to help determine the optimum dose for the next phase III clinical trial. Moreover, the protocol presents a detailed and practical methodology for future clinical trials of patent drugs developed based on TCM.

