### Randomization and blinding

A total of 240 eligible participants will be randomly allocated to the high-dose group, medium-dose group, low-dose group, or placebo group in a 1:1:1:1 ratio. Randomized sequences of each center and every packed drug were generated by an independent professor at the Drug Clinical Research Center of Shanghai University of TCM, using a stratified block randomization method with 30 blocks of block size 8 based on the PROC PLAN function of the SAS 9.2 software analysis system (SAS Institute, Cary, NC, USA).

Randomization sequences will be concealed in lightproof, sealed envelopes kept by a specified project manager and the sponsor, who are not involved in the recruitment, intervention, assessment, or statistical analysis. The treatment allocation will be blinded to the participants and investigators throughout the study, and the outcome assessors and statisticians will not be involved in the participants’ screening and allocation. Each patient will receive a unique randomized number corresponding to the drug according to the group allocation. Furthermore, the intervention group type will be replaced by the letter A, B, C, or D as blind codes of allocation. The blind codes will not be disclosed until the statistical analysis is completed. An emergency envelope has been prepared for each randomized number in each center and is to be opened for treatment only in case of medical emergency which is most probably caused by the study drug.

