### Interventions

LJGMC and the placebo are provided and manufactured by Tasly Pharmaceutical Co., Ltd. (Tianjin, China). Each LJGMC or placebo weighs 0.28 g. The production batch number is 20150101. All the drugs are packaged uniformly with the same labels. Each package, which contains 3 plus 1 days’ dosage, must be sealed and kept in a cool, dry place. The placebo, which contains no effective ingredients to treat the common cold, is almost identical to the study drug in appearance, smell, and taste. A clearly visible label on each package states “FOR TRIAL USE ONLY” and other information: name, dose, dosing schedule, indication of storage condition, expiration date, and the manufacturer’s name. An independent drug manager in each center is in charge of receiving, handling, storing, and dispensing the drugs.

Patients in the high-dose group, medium-dose group, low-dose group, or placebo-matched group will receive, respectively, 1.12 g LJGMC, 0.56 g LJGMC plus 0.56 g placebo, 0.28 g LJGMC plus 0.84 g placebo, or 1.12 g placebo each time, three times per day. All medications will be taken orally with 200 ml warm water. The treatment duration is 3 consecutive days, with a 5-day follow-up. During the study, patients will be visited four times by the investigators. Details of the study procedures are given in Table 3.

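### The trial expects to find a dose-efficacy relationship, but no named test uses dose order and the A-D codes hide that order until the analysis is over

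*Protocol article*

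**What the plan says.** - **Aim.** The Background section says of this phase II trial that "it is expected to find a dose-efficacy relationship and to help determine the optimum dose for the next phase III clinical trial". The abstract and the Discussion repeat the dose-optimisation purpose in softer words.
- **Design.** Randomization and blinding allocates patients to the "high-dose group, medium-dose group, low-dose group, or placebo group in a 1:1:1:1 ratio". Interventions sets the arms as "1.12 g LJGMC, 0.56 g LJGMC plus 0.56 g placebo, 0.28 g LJGMC plus 0.84 g placebo, or 1.12 g placebo each time", so the relative active doses are 0, 1, 2 and 4.
- **Tests.** Under Data management and statistical analysis, the primary outcome and the other durations are listed together, ending "time to fever relief, and time to fever clearance will be estimated and compared by the log-rank test". For the scores, "Comparisons among groups of TCM symptom and sign scores will be conducted using ANOVA and the Bonferroni method". For the durations, "the median time will be provided separately for each group with a two-sided 95% confidence interval". No trend version, dose score or ordered contrast is named.
- **Coding.** Under Randomization and blinding, "the intervention group type will be replaced by the letter A, B, C, or D as blind codes of allocation", and "The blind codes will not be disclosed until the statistical analysis is completed".
- **Sample size.** One intervention group is compared with placebo: 7 ± 3 days, a 2-day reduction, two-sided 0.05, 90% power. This gives 48 per group, raised to 60 for 20% drop-out.

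**The concern.** A dose-efficacy relationship is a statement about order: response improves as dose rises. A log-rank test across four groups, or a one-way ANOVA, asks only whether the groups differ somehow. Relabelling the arms at random would give the same P value. A significant result therefore does not establish a gradient, and part of the test's power goes on patterns that have nothing to do with dose.

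The coding rule makes this more than a missing detail. Any ordered test needs to know which letter is placebo and how the other three rank, and that is withheld until the analysis is over. The aim, the named tests and the blinding rule do not fit together as written. At stake is whether the dose-efficacy aim is answered by a planned inference or by reading a pattern from results whose coded form has already been seen.

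**Working it through.** **1. The plan's own figure.** n per group = 2(z₀.₉₇₅ + z₀.₉₀)² SD² / δ² = 2 × (1.960 + 1.282)² × 9 / 4 ≈ 47.3, so 48. With drop-out, 48 / (1 − 0.20) = 60. Both figures reproduce (exact t-test power at 48 is 89.8%). This calculation concerns active versus placebo only.

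**2. Ordered versus unordered test, normal-means approximation.** Inputs from the protocol: SD 3, n = 48, two-sided 0.05. The response shapes are assumptions; each gives the high dose a 2-day gain over placebo. Gains below are in days, in the order placebo, low, medium, high.

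- Unordered four-group F test: λ = n Σ(μᵢ − μ̄)² / SD², 3 and 188 df.
- Trend contrast with centred scores cᵢ: noncentrality = Σcᵢμᵢ / (SD √(Σcᵢ² / n)), 188 df.

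Equal steps (0, 0.67, 1.33, 2): Σ(μᵢ − μ̄)² = 1 + 0.111 + 0.111 + 1 = 2.222, so λ = 48 × 2.222 / 9 = 11.85 and power is 83%. With scores 0-3 the contrast matches the shape, so its noncentrality is √11.85 = 3.44 and power is 93%.

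Full effect from the low dose (0, 2, 2, 2): λ = 48 × 3 / 9 = 16 and power is 93%. With scores 0-3, Σcᵢμᵢ = 3 and Σcᵢ² = 5, so the noncentrality is 3 / (3 √(5/48)) = 3.10 and power is 87%.

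| Assumed gain (days) | Unordered | Trend, scores 0,1,2,3 | Trend, scores 0,1,2,4 |
|---|---|---|---|
| Equal steps: 0, 0.67, 1.33, 2 | 83% | 93% | 92% |
| Proportional to dose: 0, 0.5, 1, 2 | 82% | 92% | 93% |
| Rising, then flattening: 0, 1.2, 1.6, 2 | 83% | 91% | 87% |
| Full effect from low dose: 0, 2, 2, 2 | 93% | 87% | 78% |
| High dose only: 0, 0, 0, 2 | 93% | 87% | 94% |

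**3. The same comparison with the log-rank test, by simulation.** Assumptions: 48 per arm, SD 3, censoring at day 8 (3 days of treatment plus 5 of follow-up), and gamma, lognormal or normal durations.

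- Equal steps from 7 to 5 days: unordered 79 / 85 / 73%, trend (scores 0-3) 89 / 95 / 86%, in the order of the three distributions.
- Proportional to dose (7, 6.5, 6, 5 days): unordered 74-84%, trend 85-93%.
- Plateau from the medium dose (7, 6, 5, 5 days): unordered 85-91%, trend 86-94%.
- Full effect from the low dose (gamma): unordered 89%, trend 84% or 75%, depending on the scores.
- High dose only (gamma): unordered 90%, trend with scores 0-3 82%.
- No effect: the trend test rejects in 4.8-5.8% of trials.

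**4. Separating neighbouring doses.** Power ≈ Φ(δ / (SD √(2/n)) − 1.96). For δ = 1 day and n = 48: 1 / (3 √(2/48)) = 1.633, and Φ(−0.327) = 37%. For 0.5 day it is 13%; for 0.67 day, 19%. With 60 per arm, 0.5 to 1 day gives 15-45%. A 1-day difference needs 2 × 10.507 × 9 = 189.1, so 190 per arm, for 90% power. None of this depends on whether a trend test is planned.

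**The case against.** The strongest case against is that this is a condensed article. The form of the log-rank comparison, dose scores and contrasts commonly sit in an analysis plan, which is not shown, and the article does not exclude a trend version. The stated objective is efficacy and safety against placebo, with dose as a hedged addition. Per-arm medians with confidence intervals can be read in dose order once the codes open, and choosing a phase III dose does not require a significant trend P value.

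Much of this stands. Silence about a trend test would not be a finding by itself. What remains is positive text: an aim that depends on order, and a coding rule that withholds order until the analysis is finished. An ordered test in an unseen analysis plan would still have to be reconciled with that rule.

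Three stronger readings are tempting, and the documents do not support them.

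- *That unordered tests and coding are why the trial can hardly rank its doses.* Step 4 shows that this comes from a sample size set for 2 days versus placebo. A trend test detects a gradient; it does not rank neighbouring doses.
- *That the planned tests will usually miss a real gradient.* The unordered four-arm log-rank has 73-91% power in the simulated shapes. Only comparisons of neighbouring doses are that weak, and the protocol does not name those as the route to its aim.
- *That any dose statement made after the codes open is exploratory.* A test fixed in advance and run after code release is not. Lack of pre-specification makes an analysis exploratory, and that cannot be judged here.

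Nor is the trend test uniformly better: it loses power for some monotone shapes as well as for non-monotone ones.

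**Conclusion.** The point holds in a limited form. The protocol states a dose-efficacy aim, names tests that do not use dose order, and hides that order while the analysis is done, so the planned analysis as written contains no test of a dose gradient.

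The power at stake is moderate. In the log-rank simulations a trend test moves power for graded responses from about 73-85% to 85-95%; in the normal-means check the gain is roughly 4 to 11 points. Against that, power falls from about 89-93% to 75-87% if the lowest dose already has the full effect, and from about 90-93% to 82-87% if only the highest dose works and scores 0-3 are used. These figures rest on assumed response shapes, the protocol's SD of 3 days, 48 evaluable patients per arm and, for the log-rank, censoring at day 8.

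Since the true shape is unknown, the case is for adding an ordered test, not for replacing the planned ones. The comparison of active treatment with placebo is not invalidated.

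**What to change.** **Data management and statistical analysis.** Keep the planned tests. As the analysis of the dose-efficacy aim, add one pre-specified log-rank trend test (placebo < low < medium < high, scores fixed in advance) for time to all symptoms' clearance, and a linear dose contrast for the TCM scores. Report both with the three dose-versus-placebo estimates and their confidence intervals, which would show a plateau or a non-monotone pattern that the trend test handles badly.

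**Randomization and blinding.** Make the ordered test possible in one of two ways: release the letter-to-dose key after database lock with the analysis programs final, or state that the pre-specified ordered test is run immediately after code release.

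**Background and Discussion.** Describe dose selection as based on estimates, not on significant differences between doses.

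**Cost.** Wording and one more analysis; no extra patients, visits or data. The trial status section reports that recruitment is still under way. The downsides are lower power of the trend test for plateau, high-dose-only or non-monotone responses and, if the key is released at lock, earlier unmasking of the statistician. The second option avoids that earlier unmasking.

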### Participants and recruitment

We will recruit eligible participants by advertising on hospital notice boards, sending leaflets, or being recommended by doctors in outpatient clinics. A total of 240 patients will be recruited at the following seven hospitals: (1) West China Hospital of Sichuan University, (2) Shuguang Hospital Affiliated to Shanghai University of TCM, (3) First Affiliated Hospital of Guiyang College of TCM, 4) First Affiliated Hospital of Tianjin University of TCM, (5) Second Affiliated Hospital of Tianjin University of TCM, (6) Ruikang Hospital Affiliated to Guangxi University of TCM, and (7) First Affiliated Hospital of Guangzhou University of TCM. Forty patients will be recruited at each of the first two centers and 32 at each of the latter ones.

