### Change in TCM symptom and sign scores

The TCM symptom scoring system used in the study follows the *Guidelines for Clinical Research of New Chinese Medicine* [24], in which all symptoms are graded (Table 4). The change in cumulative TCM symptom and sign scores is assessed by the percentage of symptom and sign scores reduction (PSSSR), which is calculated according to the following formula: PSSSR = (scores before treatment – scores after treatment)/scores before treatment*100%. A value greater than 50% is defined as clinically effective.

**Table 4 Tab4:** Symptom and sign scoring system

Symptom	Score			
Primary	None (0)	Mild (2)	Moderate (4)	Severe (6)
Fever	<37.3 °C	37.3–37.9 °C	38.0–38.4 °C	≥38.5 °C, <39.0 °C
Pharynx uncomfortable	–	Dry pharynx	Burning pharynx	Pharynx pain
Secondary	None (0)	Mild (1)	Moderate (2)	Severe (3)
Stuffy nose	–	Heavy sound	Sometimes	Sustained
Running nose	–	Occasionally	Sometimes	Sustained
Thirsty	–	No need for water	Sometimes need water	Need water frequently
Cough	–	Occasionally	Sometimes	Frequently
Headache	–	Occasionally, mild	Sustained, moderate	Heavy, can’t insist on work
Limb pain/soreness	–	Weak, uncomfortable	Painful	Terrible, can’t stretch freely
Cumulative symptom score	Primary symptom scores + secondary symptom scores			
Sign	None (0)	Mild (1)	Moderate (2)	Severe (3)
Pharyngeal hyperemia/swelling	–	Pharyngeal mucosa hyperemia	Pharyngeal mucosa, pharynx palatine arches and uvula hyperemia	Pharyngeal swelling and heavy secretion
Total score	All symptom scores + sign score			

– No symptom

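### The score ANOVA has no baseline covariate and the log-rank test no stated stratification by centre: some precision is lost, but the analyses stay valid

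*Protocol article*

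**What the plan says.** **Randomisation.** Under Randomization and blinding: "Randomized sequences of each center and every packed drug were generated" centrally, "using a stratified block randomization method with 30 blocks of block size 8". Patients go to the "high-dose group, medium-dose group, low-dose group, or placebo group in a 1:1:1:1 ratio". The article does not name centre outright as the stratum, but it names no other factor. Participants and recruitment gives the centre sizes: "Forty patients will be recruited at each of the first two centers and 32 at each of the latter ones".

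**Time-to-event outcomes.** Data management and statistical analysis lists them in one sentence that begins with the primary outcome, time to clearance of all symptoms, and ends: "time to fever relief, and time to fever clearance will be estimated and compared by the log-rank test". Strata are not mentioned.

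**Scores.** In the same section: "Comparisons among groups of TCM symptom and sign scores will be conducted using ANOVA and the Bonferroni method". No baseline covariate and no centre term is mentioned. The outcome, which is secondary, is defined under Change in TCM symptom and sign scores as "PSSSR = (scores before treatment – scores after treatment)/scores before treatment*100", in per cent. A value above 50% counts as clinically effective.

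**The concern.** Blocking within centre balances the arms within centre. If centres differ in how long colds last, a test that leaves centre out still treats that difference as noise. Its standard error is then too large for the design, and the test is conservative.

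For the scores, a ratio to baseline is a rigid form of adjustment. It suits the data only if the post-treatment score is roughly proportional to the baseline score. From Table 4 and the entry rules, the baseline total can in theory run from about 11 (fever 2, throat pain 6, three mild secondary symptoms 3) to 33 (primary 12, secondary 18, sign 3). One point of improvement is then worth 100/11 = 9.1 percentage points at the floor and 100/33 = 3.0 at the ceiling.

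What is at stake is power, not bias. It matters most for the lower doses: the Background says that the trial looks for a dose-efficacy relationship, and effects below 2 days are where power is short.

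**Working it through.** **1. The plan's own sample size.** Inputs from Sample size: SD 3 days, difference 2 days, 90% power, two-sided 5%, drop-out 20%.

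n = 2 × (1.960 + 1.282)² × 3² / 2² = 2 × 10.51 × 2.25 = 47.3, so 48 per group. Then 48 / 0.80 = 60, and 4 × 60 = 240. The figure reproduces, and this point does not alter it.

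**2. The stratum.** 40/8 = 5 blocks at each of two centres and 32/8 = 4 blocks at each of five. That is 2 × 5 + 5 × 4 = 30 whole blocks, or 240 patients, as stated. Each arm gets 10 patients at each of the two larger centres and 8 at each of the others. Centre is the only stratum that the text supports.

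**3. Scores: ANOVA on PSSSR against ANCOVA on the post-treatment score.** The article gives no score means, SDs or correlation, so all of these are assumed: baseline mean 18, SD 4; placebo post-treatment mean 7, SD 4; effect 2.3 points; 48 per arm; one pairwise comparison at 5% without Bonferroni; no centre term; 5,000 simulated trials per row.

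| Baseline-outcome correlation | ANOVA on PSSSR | ANCOVA | Gain (points) |
|---|---|---|---|
| 0 | 69.6% | 78.5% | 8.9 |
| 0.2 | 77.4% | 80.2% | 2.8 |
| 0.3 | 81.1% | 82.4% | 1.3 |
| 0.5 | 87.6% | 89.6% | 2.0 |
| 0.7 | 91.3% | 95.9% | 4.6 |

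The pattern has a simple cause. PSSSR in effect imposes a slope of mean post-treatment score over mean baseline, here about ((7 + 4.7)/2)/18 = 0.33. With equal SDs the true slope is the correlation itself. The ratio is therefore nearly efficient around 0.3 and loses on either side.

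**4. Log-rank: unstratified against stratified by centre.** Mean 7 and total SD 3 days come from Sample size, and censoring at day 8 from 3 days of treatment plus 5 of follow-up. Assumed: gamma-distributed times, 60 per arm with no drop-out, and the centre SD. There are 3,000 simulated trials per cell. Entries are rejection rates, unstratified / stratified.

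| Centre SD (share of variance) | No effect | 1.5-day effect | 2-day effect |
|---|---|---|---|
| 0 (0%) | 5.4 / 5.0% | 71.7 / 71.7% | 92.3 / 92.3% |
| 0.5 day (2.8%) | 4.6 / 5.2% | 70.3 / 71.4% | 92.4 / 93.0% |
| 1 day (11%) | 4.6 / 5.6% | 73.4 / 76.9% | 92.8 / 94.7% |
| 1.5 days (25%) | 2.7 / 4.8% | 73.0 / 82.4% | 93.3 / 96.7% |

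A separate run at a 1-day effect gave 40.6 / 41.0%, 40.1 / 43.4% and 38.5 / 48.8% for centre SDs of 0, 1 and 1.5 days. The largest cost seen with no centre effect was 90.5 / 89.6%, in a run of 6,000 trials at the 2-day effect. Repeat runs put the unstratified type I error at centre SD 1.5 days between 2.6% and 3.8%. Monte Carlo error is about 0.5 to 1 point.

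**The case against.** The strongest objection is that the log-rank half rests on silence. A centre-stratified log-rank test is still a log-rank test, and an article often leaves strata to the full protocol or SAP, neither of which is shown. This stands. A reader might infer that the plan has decided to ignore centre, but the text supports only that stratification is not stated. The score half is firmer, because ANOVA is a named method.

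Second, a reader might infer that the scores are analysed without baseline. They are not: PSSSR is computed from each patient's baseline. For the same reason the textbook variance savings do not apply. Those are 1 − ρ² against raw post-treatment scores (9 to 49% for ρ of 0.3 to 0.7) and (1 + ρ)/2 against absolute change (35 to 15%). Neither comparator is the defined outcome. The threefold baseline range is also a theoretical floor and ceiling, not an expected spread.

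Third, the gain on the primary outcome depends on an input that the article does not give. A centre SD of 1.5 days puts 1.5²/3² = 25% of all variance between centres, which is a strong assumption. At 1 day or less the gain at the design effect is about 2 points or less. This also stands. It limits the size of the point; the direction holds, because the cost when centres do not differ is a point at most.

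Fourth, PSSSR and its 50% cut belong to a scoring system taken from a cited guideline. An efficiency argument gives no reason to demote them.

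**Conclusion.** The point holds as a low-severity matter of efficiency, with medium confidence. The design supplies a randomisation stratum and a baseline score, and the named analyses make no stated use of the first and only a rigid use of the second.

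Under the assumed inputs, ANCOVA gains about 1 to 9 power points over ANOVA on PSSSR. A centre-stratified log-rank test gains about 0 to 4 points at the 2-day effect, about 0 to 9 at 1.5 days and up to about 11 at 1 day. The correlation, score means and SDs, score effect and centre SD are all assumptions.

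A reader might infer that the primary test is invalid or that the trial is underpowered because of this. Neither follows. The unstratified test does not inflate type I error and becomes conservative when centres differ strongly. At the 2-day effect it stayed above 90% in every setting run, with 60 per arm and no drop-out.

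**What to change.** Before unblinding, make two changes to the protocol or SAP wording:

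- **Scores.** Compare the groups by ANCOVA of the post-treatment total score on treatment, baseline total score and centre. Keep Bonferroni for the pairwise comparisons. Keep PSSSR and its responder rate above 50% as defined outcomes.
- **Primary outcome.** State that the log-rank test is stratified by centre. If the SAP already says so, nothing more is needed here.

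The cost is wording only: no further patients, visits or data. ANCOVA spends seven extra degrees of freedom (one for baseline, six for centre), which is trivial with 240 patients. The stratified log-rank test loses at most about one point of power if centres do not differ. Trial status says that recruitment is under way, and the blind codes stay closed until the analysis is complete, so at that stage both changes can still be prespecified.

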#### Secondary outcomes

Secondary outcomes include time to primary symptoms and each secondary symptom disappearance, time to fever relief, time to fever clearance, and change in TCM symptom and sign scores.

Time to fever relief is defined as the time from the first dosing to time when the body temperature drops by at least 0.5 °C. Time to fever clearance is defined as the time from the first dose administration to the time when the body temperature drops below 37.3 °C and lasts for 24 hours.

In this study, all patients will be required to record their body temperature in the patient diary every 2 hours within the first 12 hours and every 4 hours during the following 12 hours. After that, if the temperature is ≥37.3 °C, it should be recorded four times at a fixed time every day, and if the temperature is lower than 37.3 °C, then there is no need to record it.

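### Bonferroni for the TCM symptom and sign scores is valid but slightly conservative; Tukey (all pairs) or Dunnett (doses versus placebo) gives the same familywise 5% with a smaller cut-off

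*Protocol article*

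**What the plan says.** The trial allocates patients to the "high-dose group, medium-dose group, low-dose group, or placebo group in a 1:1:1:1 ratio" (Protocol article, Randomization and blinding). The scores are the last of the secondary outcomes: "time to fever relief, time to fever clearance, and change in TCM symptom and sign scores" (Secondary outcomes). Their analysis is fixed in Data management and statistical analysis: "Comparisons among groups of TCM symptom and sign scores will be conducted using ANOVA and the Bonferroni method". The same section sets the general criterion: "a two-sided *P* value of <0.05 is considered to be statistically significant".

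The number of comparisons under Bonferroni is not given. Two parts of the article bear on it, and they point in different directions:

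- Sample size: "The sample size calculation is based on a comparison between the intervention group and the placebo-controlled group". This concerns the primary outcome and does not define the family for the scores.
- The end of the Background and the Discussion add a dose-finding purpose: to look for a relation between dose and efficacy and to inform the dose for phase III. Comparisons between doses can serve that purpose.

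No power is claimed for the scores.

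**The concern.** Bonferroni treats the pairwise tests as if nothing were known about how they depend on one another. In an ANOVA with four arms that dependence is known: comparisons share arms and a common error variance. Single-step procedures that use it exist for both plausible families, Tukey for all pairs and Dunnett for several treatments against one control. Each holds the familywise error at 5% with a smaller critical value than Bonferroni on the same family.

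At stake is a modest loss: some real differences on the scores are missed that an equally protective procedure would detect, and the confidence intervals are a little wider than needed. The scores are among the results that will inform the choice of dose, so even a small gain that needs no extra patients or data is worth taking.

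**Working it through.** **Inputs from the Protocol article.** Four arms, equal allocation; 60 per arm recruited, 48 per arm after the assumed 20% drop-out; two-sided 5%.

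**Assumptions.** One-way ANOVA with pooled error, so df = 4(n − 1) = 236 at 60 per arm and 188 at 48. Standardised effects d of 0.4 to 0.667 SD are assumed for the scores. The upper end borrows the primary outcome's planning ratio of 2/3 days ("The mean duration of all symptoms for the common cold was estimated to be 7 ± 3 days" and "reduction in the duration of all symptoms by 2 days is assumed to be clinically significant"). Pairwise tests are not made conditional on a significant overall F test.

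**The plan's own figure.** For the primary outcome, n = 2(1.960 + 1.282)² × 3²/2² = 47.3, rounded up to 48; 48/0.8 = 60. This agrees with "the sample size needs to be 48 cases for each group" and with 60 recruited. It is not a power statement about the scores.

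**Critical values of |t|.**
- Bonferroni, six pairs: t quantile at 1 − 0.05/12 (each pair at 0.05/6 = 0.0083).
- Tukey, six pairs: studentized range quantile for 4 groups divided by √2.
- Bonferroni, three pairs: t quantile at 1 − 0.05/6 (each pair at 0.05/3 = 0.0167).
- Dunnett, three pairs: numerical integration with correlation 0.5 between comparisons.

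| Family | Procedure | 60 per arm | 48 per arm |
|---|---|---|---|
| All six pairs | Bonferroni | 2.661 | 2.667 |
| All six pairs | Tukey | 2.587 | 2.592 |
| Three versus placebo | Bonferroni | 2.411 | 2.416 |
| Three versus placebo | Dunnett | 2.364 | 2.368 |

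**Power for one dose against placebo.** Noncentral t with noncentrality d√(n/2).

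| n per arm | d | Bonferroni, 6 | Tukey, 6 | Bonferroni, 3 | Dunnett, 3 |
|---|---|---|---|---|---|
| 60 | 0.4 | 32.2% | 34.8% | 41.4% | 43.3% |
| 60 | 0.5 | 53.2% | 56.1% | 62.9% | 64.6% |
| 60 | 0.6 | 73.4% | 75.7% | 80.9% | 82.1% |
| 60 | 0.667 | 83.8% | 85.5% | 89.2% | 90.0% |
| 48 | 0.4 | 24.3% | 26.7% | 32.7% | 34.4% |
| 48 | 0.5 | 41.6% | 44.5% | 51.5% | 53.3% |
| 48 | 0.6 | 60.8% | 63.6% | 70.0% | 71.6% |
| 48 | 0.667 | 72.5% | 74.9% | 80.2% | 81.4% |

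**Like-for-like gain.** Tukey over six-pair Bonferroni: 1.7 to 2.9 points. Dunnett over three-pair Bonferroni: 0.9 to 1.9 points. As sample-size ratios at 80% power and 60 per arm:
- six pairs: (2.661 + 0.842)²/(2.587 + 0.842)² = 1.04
- three pairs: (2.411 + 0.842)²/(2.364 + 0.842)² = 1.03

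Interval widths shrink by 1 − 2.587/2.661 = 2.8% and 1 − 2.364/2.411 = 1.9%.

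**Change of family.** Six-pair Bonferroni to Dunnett gives (2.661 + 0.842)²/(2.364 + 0.842)² = 1.19. Going from six to three Bonferroni comparisons alone gives (2.661 + 0.842)²/(2.411 + 0.842)² = 1.16, so most of the 1.19 comes from dropping tests. In power this is 9 to 11 points at 60 per arm for d of 0.4 to 0.6 (6 points at 0.667), and 9 to 12 points at 48 per arm.

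**Familywise error, 400,000 simulated null trials, 48 per arm.**

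| Procedure | Over three versus placebo | Over all six |
|---|---|---|
| Bonferroni, 6 | 2.3% | 4.1% |
| Tukey | 2.8% | 5.0% |
| Bonferroni, 3 | 4.4% | 7.7% |
| Dunnett | 5.0% | 8.6% |

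Tukey and Dunnett each use the full 5% on their own family; Bonferroni stops at 4.1% and 4.4%.

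**The case against.** The strongest reply is that this is a preference, not an error. Bonferroni is valid, the scores are secondary, no power is promised for them, and no figure or passage is contradicted. The family of comparisons is a detail that an article may leave to the analysis plan, which is not shown. Bonferroni also needs no assumption about how the tests are correlated, while Tukey and Dunnett are exact only with normal errors, equal variances and equal group sizes. The score measure is a percentage reduction capped at 100%, with missing values carried forward, so those conditions may hold only roughly.

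Most of this stands, and it limits the point to an efficiency improvement. The distributional argument weakens it less than it seems: the article already commits to ANOVA, and Bonferroni tests built on that ANOVA's pooled error rest on the same normal, equal-variance model. Unequal group sizes are handled by the Tukey-Kramer form.

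A reader might infer something stronger: that the plan tests all six pairs, that dose-versus-dose tests waste error, and that Dunnett would keep the same error rate while raising power from 73% to 82% (60 per arm, 0.6 SD), worth about 19% more patients. The article does not support this. It never states six pairs. Its dose-finding aim gives dose-versus-dose comparisons a purpose. And Dunnett protects only the comparisons with placebo: its cut-off applied to all six pairs gives 8.6% familywise error, against 4.1% for six-pair Bonferroni.

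**Conclusion.** The point holds as a minor improvement. Whichever family the sponsor meant, a procedure with the same familywise 5% and a smaller critical value is available under the planned ANOVA. The gain on the same family is about 2 to 3 power points with Tukey or 1 to 2 with Dunnett, equivalent to 3 to 4% more patients, with intervals 2 to 3% narrower.

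This rests on a one-way pooled-error ANOVA, 48 to 60 patients per arm and assumed effects of 0.4 to 0.667 SD. The critical values do not depend on the assumed effects; the power figures do. The larger difference between six-pair Bonferroni and Dunnett is the price of formal dose-versus-dose tests, and should be presented as a design choice rather than as the same protection with more power.

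**What to change.** In Data management and statistical analysis, replace the reference to Bonferroni with one of these, according to the family intended:

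- **Dose-versus-dose tests wanted, as the dose-finding aim suggests:** all pairwise differences in the scores will be tested by Tukey's procedure (Tukey-Kramer if group sizes differ) at familywise 5%, with simultaneous 95% confidence intervals.
- **Only dose versus placebo intended:** each dose will be compared with placebo by Dunnett's two-sided procedure at familywise 5%, with simultaneous 95% confidence intervals; differences between doses will be reported as estimates with 95% confidence intervals and not formally tested.

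The cost is one line of wording, settled before unblinding. Both procedures are standard in SAS, which the trial already uses, and no extra patients or data are needed. The first option gives up nothing that six-pair Bonferroni protects. If six pairs were intended, the second gives up formal tests between doses.
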